### Control group

The control group will receive a mandatory introductory lecture on the positive effects of physical activity on the incidence and prognosis of breast cancer. Afterwards all participants will be given a brochure providing the most important facts on this topic.

Contrary to the intervention group, no training and no physical activity diaries will be provided. Changes in physical activity behavior are measured identically to the interventional group through questionnaires (IPAQ at SE–V4) and examinations of physical capacity (VO_2_ peak) at time points SE, V1, and V2.

Additionally, a dietitian-led nutrition group lesson on healthy eating will be held for the control group. During this lesson the subjects receive general information based on the recommendations of the German Society of Nutrition, which is referred to as “usual care in Germany” in this study. Eating habits will be recorded identically as in the intervention group via validated questionnaires (EPIC-FFQ and MEDAS) at the defined time points SE, V1, V2, V3, and V4.

The psychological guidance of the control group consists of an explanation of the psychological data entry forms which are given to the study participants. An explicit psycho-oncological intervention strategy is also not intended in this group. The participants will be informed that changes in daily routine concerning physical activity and dietary habits among other things should resolve in improvement of quality of life, a reduction of stress, and a more optimistic approach to the future. In order to verify this, the participants will receive questionnaires (TICS, LOT-R, EORTC QLQ-C30/-BR23, and BKAE for registration of changes in attitude towards physical activity and MD) at SE and V1–V4. The psychological information of the control group corresponds to that of the intervention group.

### Measurements

In order to achieve the study goals and to answer the research questions, structured questionnaires and interview sheets, diaries, clinical and instrument-based examinations, as well as blood and stool tests will be used. These are listed and described in the following sections.

#### Medical history

Data will be gathered by means of an interview at study enrollment (SE). In addition to a basic clinical assessment, pre-existing internal and gynecological illnesses, and general risk and protective factors such as body weight, alcohol consumption, nutritional behavior, level of activity, and number of pregnancies will be assessed.

#### Sociodemographics

This will also be collected at SE. The psychosocial and socioeconomic risk and protective factors such as living conditions, job situation, and income level will be assessed.

#### Medical radiation exposure

Data will be gathered by means of an interview at SE. The previous diagnostic and therapeutic radiation exposure will be documented.

#### Study satisfaction questionnaire

This will be handed out at V1, V2, V3, and V4. Questions will capture the subject’s acceptance of the study, their satisfaction with the supervision, an evaluation of the physical activity and nutrition program, and their assessment of the everyday practicality of the intervention program.

#### Cardiovascular assessment

Within this examination at time points SE and V1–V4, the patient’s medical history is taken and a clinical examination with focus on the cardiovascular system will be performed. A resting electrocardiogram (ECG), pulmonary function testing, and blood pressure measurements are obligatory. Resting heart rate and blood pressure are recorded as measuring parameters.

#### Exercise testing/spiroergometry

Spiroergometry is an objective and well-known examination for assessment of the cardiopulmonary system, as it measures the respiratory gases under exercise stress. As the maximal oxygen uptake and the aerobic and anaerobic respiratory capacity are measured, the results enable a precise statement about the maximum cardiopulmonary capacity as well as aerobic and anaerobic capacity. The target parameters VO_2_ peak as well as VO_2_ at ventilatory aerobic and anaerobic thresholds (VT1 and VT2) [23] provide information on the fitness level at visits SE, V1, and V2.

#### International Physical Activity Questionnaire

The International Physical Activity Questionnaire (IPAQ) comprises five areas of activity, which are examined independently of each other [24]. The questionnaire is a simple instrument which can be used to collect internationally comparable data for health-promoting physical activity. The aim is to assess different modes of physical activity performed in daily life. The questionnaire relates to the time which has been spent on physical activity during the last seven days. Activities within the scope of occupational, household, and garden tasks and moving between destinations are included as well. The IPAQ is assessed at all study time points (SE, V1–V4).

#### Examination of physical constitution

The examination of physical constitution comprises the documentation of anthropometric parameters such as height, body weight, waist, hip, and upper arm measurements, skinfold tests, and the bioelectric impedance analysis (BIA) measurement at visits SE, V1, V2, V3, and V4. These measurements serve to record the percentage of body fat, BMI, and level of muscle mass and body water.

#### Blood tests

Within the context of the study, various blood values are determined (Table 2). Blood values are measured in the intervention group as well as in the control group at the time points (SE, V1–V4).

**Table 2 Tab2:** Blood measurements

Routine blood parameters measured in recruiting centers: • Glutamate pyruvate transaminase (GPT), alanine aminotransferase (ALT) • Total cholesterol • High-density lipoprotein (HDL) cholesterol • Low-density lipoprotein (LDL) cholesterol • Triglycerides • Glucose • Blood cell count • Gamma-glutamyl transferase (GGT)
Blood parameters measured in central or special laboratories: • Insulin • Proencephalin A 119 D159 (Sphingotec GmbH) • Proneurotensin 1–117 (Sphingotec GmbH) • High-sensitivity C-reactive protein (hsCRP) • Omega-3, 6, and 9 fatty acid content in the membrane of erythrocytes

#### Stool tests

The subjects in the intervention group as well as in the control group take stool samples at home at the five time points (SE, V1–V4). A collective microbiome and metabolome analysis is carried out at a later date.

#### EPIC Food Frequency Questionnaire

The EPIC Food Frequency Questionnaire (EPIC-FFQ) [25–27] refers to food consumption during the past year and covers 148 food items. For each item questions are asked concerning the average quantity consumed (predefined servings) and the frequency of consumption (one to six times per day, week, month, or year). Color photos simplify the definition of serving sizes for food items which are not consumed in normal household quantities. Furthermore, the participants are specifically asked about their use of cooking fats/oils, the frequency of consumption of sauces with meat and fish, the fat content of the milk they consume, the use of sugar and milk in coffee and tea, and the seasonal consumption of fresh fruit and vegetables. The data input and questionnaires are evaluated via the study management system (SMS) for health research, which has been developed and supervised by the Department of Epidemiology of the German Institute of Human Nutrition Potsdam-Rehbruecke (DIfE). The EPIC-FFQ is conducted at all five time points (SE, V1–V4) in both the intervention group and the control group.

#### Mediterranean Diet Adherence Screener

The Mediterranean Diet Adherence Screener (MEDAS) [28] was developed within the scope of the PREDIMED study and is an instrument used to determine the extent to which the Mediterranean dietary pattern is adhered. It comprises 14 questions. The evaluated Spanish version was translated into German for the LIBRE study and complemented by pictures of serving sizes. The German version of the MEDAS will be validated within the scope of the pilot study. The MEDAS questionnaire is conducted at all five time points (SE, V1–V4) in both the intervention and the control group and at time points V1-6 and V1-9 in the intervention group.

#### Measurement of quality of life

In order to acquire information on health-related quality of life (HRQOL), a composed questionnaire from the European Organisation for Research and Treatment of Cancer (EORTC), comprising a 30-item core questionnaire (QLQ-C30) and a 23-item breast cancer module (QLQ-BR23), is used before and after the intervention [29, 30]. Accordingly there are reference values by Scott et al. [31] which are of great importance for comparing our data. The advantage of the QLQ-C30/-BR23 is on one hand its present-day relevance and on the other hand its validation for breast cancer (QLQ-BR23). We formulate the hypothesis that regular physical activity and the implementation of healthy nutrition (intervention group) can lead to a general and specific improvement in HRQOL. The 53 questions focus on cognitive, social, emotional, and physical functioning, and one scale evaluates the global health status in general. Three other scales estimate fatigue, pain, as well as nausea and vomiting, and six single items measure dyspnea, insomnia, appetite loss, constipation, diarrhea, and financial difficulties. The breast cancer-specific module QLQ-BR23 comprises 23 multiple and single items assessing disease symptoms (breast and arm symptoms, upset caused by hair loss and systemic therapy side effects) as well as addressing body image, sexual functioning, and future perspectives. Validation studies in European countries and the USA have been conducted within a cross-cultural context [32].

#### Measurement of optimism (Life Orientation Test-Revised)

The Life Orientation Test-Revised (LOT-R) [33] is developed to collect individual differences of generalized optimism versus pessimism in the form of a personality variable. It has been applied in various intervention studies which, among other things, look at the consequences of dispositional optimism on behavior, emotion, and physical health. We also formulate the hypothesis that regular physical activity and the implementation of healthy nutrition (intervention group) can lead to a more optimistic attitude to life.

#### Measurement of chronic stress (Trier Inventory for Chronic Stress) [34]

The Screening Scale for Chronic Stress (SSCS) included in the Trier Inventory for Chronic Stress is a 12-item (short version) questionnaire which measures five different aspects of chronic stress: lack of social recognition, business pressures, social stress, chronic anxiety, and overburdening [34]. One can hypothesize that regular physical activity and the implementation of healthy nutrition (intervention group) can lead to a reduction in the individual perception of stress and to better stress management. The SSCS questionnaire has been well examined on a test statistical basis and shows good variables for quality criteria.

#### Measurement of attitudes and views on physical exercise and healthy eating

It is established in social-psychological attitude research that a person’s positive attitude towards lifestyle (here regular exercise and healthy eating) does not in itself correspond to an equivalent everyday behavior (i.e., to really eat healthfully and practice regular sports or exercise). Most people take a positive view of prevention such as cancer screening, but de facto only a small number of people actively make use of cancer prevention measures. Therefore, for the present LIBRE study, above all due to the question of the practicability of the intervention program in the sense of good compliance, it is important to ask about the attitudes towards lifestyle changes. In particular, we are interested in two questions. (1) What are the predictors of regular participation in preventive measures (sport, nutrition)? (2) Are attitudes, subjective norms, or perceived behavior control towards a behavior relevant for the intention of behavior (i.e., to train regularly and to eat healthfully) and for the de facto behavior shown? To answer these questions, we developed a new questionnaire based on the theory of planned behavior according to Fishbein and Ajzen [35]. This theory maintains that the best predictors for planned and deliberate behavior are the intentions related to behavior. Behavioral intentions are defined by attitudes towards a behavior, subjective norms, and perceived behavior control. The theory of planned behavior has been examined in many studies dealing with health psychology (e.g., surgery intentions, food adherence, and physical activity behavior among others) [36–40].

The questionnaire Evaluation of Physical Activity and Nutrition (Bewertung koerperlicher Aktivitaet und Ernaehrung, BKAE) contains questions which are divided into two sections: physical activity and regular healthy nutrition. Each section has four scales (two attitudes, subjective norms, and perceived behavior control) and two innovative single items (past behavior and factor time and guidance). All questions are measured on seven-point Likert scales and, to avoid conformational bias, several statements are reverse scaled.

### Study endpoints

The trial employs three independent co-primary endpoints: (1) the adherence to the Mediterranean diet measured by the MEDAS score, (2) the BMI, and (3) the ventilatory threshold VT1 measured in spiroergometry as a parameter of physical fitness one year after the structured intervention program.

Secondary endpoints of the study are, among others, the measurements of quality of life (EORTC QLQ-C30-/BR23), stress coping (TICS), optimism grade (LOT-R), fat calorie intake (EPIC-FFQ), maximal oxygen intake (VO_2_ max), and physical activity (IPAQ) over time (see Table 3 for details).

**Table 3 Tab3:** Primary, secondary, and other outcome measures

Primary outcome measures: • Mediterranean Diet Adherence Screener (MEDAS) score • Body mass index (BMI) • Ventilatory threshold 1 (VT1) determined by bicycle spiroergometry For all three outcome measures, the change between baseline and 12 months will be analyzed. Secondary outcome measures: Psychology: • Stress coping capacity, as measured by the Trier Inventory for Chronic Stress (TICS) questionnaire • Grade of optimism, as measured by the Life Orientation Test (LOT) questionnaire • Quality of life, as measured by the European Organisation for Research and Treatment of Cancer Quality of Life Questionnaire-Core 30 (EORTC QLQ-C30) Physical activity: • Maximum oxygen consumption (VO_2_ peak), as measured by spiroergometry • Oxygen consumption (VO_2_) and watts at ventilation threshold 1 (VT1 and VT2), as measured by spiroergometry • Physical activity, as measured by the International Physical Activity Questionnaire (IPAQ) Nutrition: • Mediterranean Diet Adherence Screener (MEDAS) score • Dietary habits and calorie intake, as measured by the European Prospective Investigation into Cancer and Nutrition Study Food Frequency Questionnaire (EPIC-FFQ) • BMI Breast cancer incidence and mortality • Breast cancer incidence • Overall and breast cancer mortality rate Other outcome measures: • Attitudes and beliefs regarding physical training and healthy diet, as measured by the “Bewertung koerperlicher Aktivitaet und Ernaehrung” (BKAE) questionnaire • Satisfaction with the study • Body fat content, as measured by skinfold measurement • Tobacco and alcohol consumption • Omega 3, 6, and 9 fatty acids in the erythrocyte membrane • Serum cholesterol including serum high- and low-density lipoprotein cholesterol • Serum triglycerides, glucose, high-sensitivity C-reactive protein, and insulin • Serum proenkephalin and proneurotensin • Hospitalization days for breast cancer If appropriate, secondary and other outcome measures will be analyzed as the change from baseline over time of all available time points.	

### Sample size, randomization, and statistical analysis

The following differences of the three co-primary endpoints between study arms one year after the structured intervention are considered clinically relevant and achievable: 1 point increase in the MEDAS score, 1 kg/m^u^ reduction in BMI, 1 ml/min/kg increase in the ventilatory threshold VT1. In order to detect these differences in a two-sided *t* test with expected standard deviations as observed in the LIBRE feasibility study, a minimum of 490 evaluable patients are required with a Bonferroni adjusted significance level of 0.05/3 per single endpoint and a power of 90 %. The final sample size was set to a total of 600 patients to be enrolled to account for a drop-out rate of at least 15 %.

Randomization is performed with a 1:1 ratio using an Internet-based central randomization system based on a modified version of Pocock’s minimization algorithm, stratifying for center, disease status (no prior breast cancer, prior breast cancer without contralateral prophylactic mastectomy, prior breast cancer with contralateral mastectomy), age (<50 versus ≥50 years), physical activity as measured by the IPAQ (<24 versus ≥24 MET-h/week), BMI (<25 versus ≥25 kg/m^2^) [41].

The primary endpoints will be assessed using analysis of variance adjusting for possible differences in baseline characteristics. No interim analyses will be conducted. A written statistical analysis plan describing all planned primary and secondary endpoint analyses in detail will be set up prior to the start of data analysis.

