**Methods/design:**

This multicenter, interdisciplinary, prospective, two-armed, randomized (1:1) controlled trial aims to enroll a minimum of 600 *BRCA1* and *BRCA2* mutation carriers to partake in either a lifestyle intervention or usual care. The study primarily aims to demonstrate an improvement of nutritional behavior (adherence to the Mediterranean diet), body mass index, and physical fitness. Furthermore, the effects on quality of life, stress coping capacity, breast cancer incidence, and mortality will be investigated. The intervention group (IG) will receive a structured lifestyle intervention over 12 months, whereas the control group (CG) will only receive information regarding a healthy lifestyle. During the first 3 months, women in the IG will receive structured, individualized, and mainly supervised endurance training with a minimum of 18 MET-h physical activity per week and nutrition education based on the Mediterranean diet. Over the following 9 months, IG monthly group training sessions and regular telephone contacts will motivate study participants. The CG will receive one general training session about healthy nutrition in accordance with the recommendations of the German Society of Nutrition (standard of care in Germany) and the benefits of regular physical activity on health status. At randomization and subsequent time points (3 and 12 months), cardiopulmonary fitness will be assessed by spiroergometry, and nutritional and psychological status will be assessed by validated questionnaires, interviews, and clinical examinations.

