### Participants

The goal is to recruit a minimum of 600 patients. Recruitment and study conduct take place at 18 centers of the German Consortium for Hereditary Breast and Ovarian Cancer (GC-HBOC). Table 1 details the study’s inclusion and exclusion criteria.

**Table 1 Tab1:** Study population: inclusion and exclusion criteria

Inclusion criteria (all criteria must apply): • Women with a *BRCA1* or *BRCA2* germline mutation • Age over 18 years • Written informed consent
Exclusion criteria: • Ongoing chemo- or radiation therapy (recruitment is possible 6 weeks after completing therapy) • Metastatic tumor disease • Expectancy of life <3 years • Limited cardiovascular and lung diseases (unstable CHC, heart failure stage IV, chronic obstructive pulmonary disease GOLD IV, maximal blood pressure at rest >160/100 mmHg) • Significant orthopedic problems not allowing exercise • Serious diseases not allowing a participation in group interventions (e.g., psychiatric or internal ailment) • Karnofsky index <60 % • Women with an exercise capacity <50 watts • Food allergies not allowing consumption of a Mediterranean dietary pattern • Vegans • BMI <15 kg/m^2^ • Pregnancy • Insufficient knowledge of the German language • Lack of compliance • Current participation in other lifestyle intervention trials

*CHC* Coronary Heart Condition

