#### Nutrition

Within the framework of the LIBRE study, the nutrition intervention is based on the principles of a Mediterranean dietary pattern (MD). Furthermore, obese patients (BMI ≥30 kg/m^2^) are instructed to limit their energy (kilocalorie) intake. Nutrition intervention in the intervention group begins with an intensive 3-month nutrition program during which biweekly nutrition courses led by dietitians take place in groups. The group course includes a cooking class and a guided tour of a supermarket. At the end of the first 3 months, the nutrition courses take place at monthly intervals for the remaining course of the first study year. The main objective of the nutrition intervention is to provide practical nutritional training, which should enable the subjects to achieve a long-term change in their eating habits, replacing former eating habits with the MD. Eating habits are recorded using validated questionnaires (the European Prospective Investigation into Cancer and Nutrition Food Frequency Questionnaire [EPIC-FFQ] and Mediterranean Diet Adherence Screener [MEDAS]) at the time points SE, V1, V2, V3, and V4. Participants of the intervention group additionally received the MEDAS questionnaire at time points V1-6 and V1-9.

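### The sample size and the named primary ANOVA treat all women as independent, although only the intervention arm is treated in groups; 90% power is therefore not assured

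*Protocol article*

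**What the plan says.** All references are to the Protocol article.

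- **Sizing** (Sample size, randomization, and statistical analysis). The calculation compares individual women by a t test, two-sided, at 90% power. The basis given is "expected standard deviations as observed in the LIBRE feasibility study, a minimum of 490 evaluable patients are required". Multiplicity over the three co-primary endpoints is handled by a "Bonferroni adjusted significance level of 0.05/3 per single endpoint". Enrollment is set at 600 to cover drop-out of at least 15%. No ICC, group size or design effect is given.
- **Analysis** (same section). The primary endpoints go into an analysis of variance adjusted for baseline differences. Details are deferred to a separate analysis plan. Women are randomized individually, and center is a minimization factor.
- **Intervention arm.** Under Nutrition, "biweekly nutrition courses led by dietitians take place in groups" for three months, with a cooking class and a supermarket tour, then monthly courses for the rest of the year. For the following nine months the abstract says "IG monthly group training sessions and regular telephone contacts will motivate study participants". Table 1 excludes women whose illness prevents group participation.
- **Control arm** (Control group). One introductory lecture and one dietitian-led group lesson.
- **Setting** (Participants). "Recruitment and study conduct take place at 18 centers".

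**The concern.** Women who attend the same courses and sessions for a year share teaching, discussion and peer influence. Their 12-month outcomes may then be more alike than those of women in different groups. Controls have almost no such shared exposure, so any correlation sits in one arm only.

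A two-sample t test, or an ANOVA without a group term, counts 245 intervention women as 245 independent pieces of information. With a positive within-group correlation there are effectively fewer. The stated power is then too favorable, and a standard error that ignores the grouping is too small. MEDAS and BMI are the most exposed co-primary endpoints, because the group nutrition program targets them directly.

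**Working it through.** **Inputs from the protocol.** Two-sided alpha 0.05/3 = 0.0167 per endpoint; power 90%; difference of 1 unit on each endpoint (for example "1 point increase in the MEDAS score"); 490 evaluable, so 245 per arm; 600 enrolled; 15% loss; 18 centers.

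**Assumptions, not in the documents.** ICC 0.01 to 0.05; group size m = 6 to 14. The upper group size is roughly one group per center: 245/18 = 13.6.

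**Step 1: the plan's own figure.** The standard deviations are not printed, so 490 cannot be reproduced independently. Solving backwards, z(1 − alpha/2) = 2.394 and z(0.90) = 1.282, with sum 3.676. Then SD = √(245/2)/3.676 = 3.01 for a difference of 1 (3.00 with the t distribution). An SD near 3.0 returns 245 per arm with no design effect. So 490 is consistent with no clustering allowance, but this is circular and does not prove it.

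**Step 2: reserve from the enrollment target.** 490/0.85 = 576.5, so 577 would suffice, and 600 × 0.85 = 510 evaluable. Power at 510 without clustering is 91.2%. The reserve covers a variance inflation of 510/490 = 1.041. With groups of 8 that is an ICC of 2 × 0.041/7, about 0.012.

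**Step 3: clustering in the intervention arm only.**

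- Variance inflation of the contrast: VIF = [1 + (m − 1) × ICC + 1]/2
- Power at 490: Φ(3.676/√VIF − 2.394)
- Power at 510: Φ(3.750/√VIF − 2.394), since 3.676 × √(510/490) = 3.750
- Type I error if grouping is ignored: 2 × Φ(−2.394/√VIF)

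| m | ICC | VIF | Power at 490 | Power at 510 | Type I error per endpoint |
|---|---|---|---|---|---|
| 6 | 0.01 | 1.025 | 89.2% | 90.5% | 0.018 |
| 6 | 0.05 | 1.125 | 85.8% | 87.3% | 0.024 |
| 8 | 0.01 | 1.035 | 88.9% | 90.2% | 0.019 |
| 8 | 0.05 | 1.175 | 84.1% | 85.7% | 0.027 |
| 10 | 0.02 | 1.090 | 87.0% | 88.4% | 0.022 |
| 10 | 0.05 | 1.225 | 82.3% | 84.0% | 0.031 |
| 14 | 0.01 | 1.065 | 87.9% | 89.2% | 0.020 |
| 14 | 0.05 | 1.325 | 78.8% | 80.6% | 0.038 |

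Power refers to the endpoint that drives the sample size. The type I error column assumes a zero average effect with effects that differ between groups.

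**Step 4: family-wise error.** Three times the per-endpoint error gives a Bonferroni bound of 3 × 0.018 = 5.4% up to 3 × 0.0375 = 11.3%, against the intended 5%.

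**The case against.** A reader might infer that the trial fails to deliver 90% power and that its standard errors are wrong. The documents do not support that. ICC and group size are unknown, and at ICC 0.01 with groups of up to 8 the 510 evaluable women still reach about 90%. This stands, so the point is conditional.

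A reader might also blame the 18 centers. A center main effect is not the problem: center is a minimization factor, so it largely cancels in the comparison, and leaving it out tends to be conservative. Only variation between intervention groups, or in the program effect between centers, inflates the variance.

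Other objections stand in part:

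- **Type I error.** If the program affects nobody, individual randomization keeps the comparison valid. The inflation arises only when the average effect is zero but effects differ between groups.
- **Individual components.** Under Physical activity, each woman has her own training plan, and months 4 to 12 are mainly home-based. The correlation may therefore be lower for VT1. The article does not say that groups are closed or that staff stay the same.
- **Offsets.** The t-test sizing takes no credit for baseline adjustment, which may recover some power. It does not remove correlation that arises after randomization. An endpoint with a smaller SD than the driving one has spare power.
- **Deferred analysis plan.** It may add a group effect, and whether it does cannot be judged here. It cannot cure the sample-size basis, which this article already fixes without a clustering allowance.

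**Conclusion.** The point holds in conditional form. The sizing and the named analysis assume independence in a partially nested design, and the article states no reason why clustering can be ignored. For any positive correlation within intervention groups, or variation of the program effect between centers, the direction is clear: less power than an independence calculation gives, and an unadjusted standard error that is too small.

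The size is uncertain. It is negligible for small groups with ICC near 0.01. At ICC 0.05 power falls to about 86% with groups of 6 and 79% with groups of 14, at 490 evaluable and before any gain from baseline adjustment. These figures rest on the assumed ICC and group sizes, equal group sizes, equal total variance in both arms and a normal approximation.

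**What to change.** 1. Record the intervention group each woman attends, for nutrition and for training if these differ. The trial is still recruiting, so this can be captured prospectively.
2. Fit the baseline-adjusted primary model with a random intervention-group effect in the intervention arm only, treating controls as ungrouped. A random center-by-arm effect is the alternative. Use small-sample degrees of freedom (Satterthwaite or Kenward-Roger).
3. State the expected group size and replace the flat 90% with power over a range of ICC and group size, per endpoint, with the feasibility-study SDs.

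The cost is one extra variable, some analysis-plan wording, slightly wider intervals and a less favorable stated power. No additional patients are required.

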A limitation of the trial might occur during randomization, especially for highly motivated participants. They may be disappointed if randomized to the control arm, and therefore may withdraw from the study or exercise nonetheless. In addition, cross-over communication regarding the Mediterranean dietary pattern between the intervention and control group cannot be completely avoided. On the other hand, it might be difficult for less motivated working women or mothers to integrate the exercise program into their everyday life.

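### The primary ANOVA of 12-month change leaves the 3-month values unused and, unless values are imputed, omits women without a 12-month visit; a repeated-measures model would be a cheap improvement

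*Protocol article*

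**What the plan says.** **Primary method.** Under the heading on sample size, randomization and statistical analysis, the protocol article states: "The primary endpoints will be assessed using analysis of variance adjusting for possible differences in baseline characteristics". Table 3 sets the variable for all three co-primary endpoints as the change from baseline to 12 months. The same table says that secondary and other outcomes will, where appropriate, be analysed over every visit with data.

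**Sample size.** The article states that "a minimum of 490 evaluable patients are required", with a "Bonferroni adjusted significance level of 0.05/3 per single endpoint and a power of 90" per cent, a target difference of one unit on each endpoint and "expected standard deviations as observed in the LIBRE feasibility study". Enrolment is set at 600 to allow for drop-out of 15% or more.

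**Measurements.** MEDAS (section on the Mediterranean Diet Adherence Screener), weight and BMI (section on physical constitution) and VT1 (section on exercise testing) are all scheduled at study entry (SE), 3 months (V1) and 12 months (V2) in both arms. MEDAS is also collected at V1-6 and V1-9, but only in the intervention arm.

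**Withdrawal.** The Discussion says of highly motivated women: "They may be disappointed if randomized to the control arm, and therefore may withdraw from the study or exercise nonetheless". It adds that less motivated women may find the exercise programme hard to fit into daily life, and that dietary advice may pass between the arms.

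**Deferred detail.** A SAP covering all primary and secondary analyses is to be written before data analysis starts. It is not at hand.

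**The concern.** A change score needs both of its values. If nothing is imputed, a woman without V2 has no change score and does not enter the analysis of variance, even if she attended at 3 months. The article plans for drop-out of 15% or more and names a mechanism that would act in one arm only. Yet its statistical section treats drop-out only as lost numbers, to be made up by enrolling more women.

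Motivation plausibly affects diet, weight and fitness. If motivated women leave the control arm, the remaining controls may look worse than the randomised control arm would have looked, and the arm difference would be overstated. The 3-month value may carry information about who leaves and how she would have fared, but the primary method as published does not use it.

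**Working it through.** **1. The plan's own figures.** For two means with 1:1 allocation, n per arm = 2(z₁₋α/₂ + z₁₋β)²σ²/δ².

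- α = 0.05/3 = 0.01667 two-sided, power 0.90 and δ = 1 are from the article. The SD is not printed, so 490 cannot be reproduced independently.
- Solving for σ with 245 per arm: σ = √(245/2) / (2.394 + 1.282) = 3.01 (3.00 with the noncentral t distribution).
- In the other direction, σ = 3.0 gives 488 in total and σ = 3.01 gives 490. The figure is plausible if the endpoint that drives it has an SD of about 3.
- Drop-out: 490/0.85 = 577, so 600 covers 15%. At 15%, 600 × 0.85 = 510 remain. The limit is 600 − 490 = 110 women, and 110/600 = 18.3%.

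There is no arithmetic error. The point concerns the analysis method.

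**2. A simple illustration.** If a share p of controls leave and would have improved by d more than those who stay, the mean of the remaining controls understates the full control-arm mean by p × d. Assuming p = 20% and d = 1 MEDAS point gives 0.20 × 1 = 0.2 points, a fifth of the 1-point target. Halving both assumptions gives 0.10 × 0.5 = 0.05 points. Neither p nor d comes from the article.

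**3. Simulation of the two methods.** The assumptions, none of them article figures except the 1-unit effect, are:

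- 300 women per arm, true effect 1.0 at 3 and 12 months, SD 3, with higher values better.
- Correlation 0.6 with baseline and 0.7 between 3 and 12 months.
- Loss of 25% of controls (75 women) and 11.7% of the intervention arm (35 women), together 110/600 = 18.3%.
- Better-scoring women more likely to leave the control arm and worse-scoring women more likely to leave the intervention arm. Both selections favour the intervention, so this is a deliberately adverse case.

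The completer estimate is the arm coefficient from regressing the 12-month value on arm and baseline. With baseline in the model, this gives the same arm effect as analysing the change. The repeated-measures (maximum likelihood) estimate is b₂ + γb₁. Here b₁ is the baseline-adjusted arm effect at 3 months in all women seen then. In completers, b₂ and γ are the coefficients of arm and of the 3-month value for the 12-month value, given baseline.

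| Loss depends on | Share of losses before 3 months | Completers | Repeated measures |
|---|---|---|---|
| chance | none | 1.00 | 1.00 |
| baseline value | none | 1.00 | 1.00 |
| 3-month value | none | 1.34 | 1.00 |
| 3-month value | half | 1.33 | 1.13 |
| 3-month value | all | 1.34 | 1.34 |
| unseen 12-month value | none | 1.63 | 1.46 |
| unseen 12-month value | all | 1.63 | 1.63 |

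Under random loss the empirical standard errors were 0.218 and 0.214. With correlations varied from 0.3/0.4 to 0.8/0.9 and no loss before 3 months, the 3-month mechanism gave 1.26–1.34 (completers) against 0.99–1.00 (repeated measures). The 12-month mechanism gave 1.36–1.88 against 1.18–1.78.

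**4. Reading.** The repeated-measures estimate was no more biased than the completer estimate in any of these scenarios. It removed the bias only where observed values explained the loss, reduced it in part where they explained it in part, and gained nothing where the loss came before V1.

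**The case against.** **Nothing restricts the analysis to completers.** A reader might infer that the primary analysis is limited to evaluable women. The article does not say so. The word appears only in the sample-size sentence, where it means the number left after drop-out. No analysis set and no missing-data rule is given, and both are ordinary SAP content. This stands in full: their absence from a condensed article is no finding.

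**The Discussion is cautious.** A reader might also infer that the authors predict opposite selection in the two arms and hence bias in favour of the intervention on every co-primary endpoint. The text says only that motivated controls may withdraw, without a rate. For less motivated women it mentions difficulty, not withdrawal. It also says that controls may exercise anyway and that dietary advice may cross between arms, both of which would shrink the difference. This stands too.

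**The remedy may miss the named mechanism.** Disappointment follows randomisation, so these women may leave before 3 months, where the repeated-measures model gains nothing. This stands, and is why a sensitivity analysis belongs with it.

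**The method is conventional, and the 3-month data are used elsewhere.** A baseline-adjusted analysis of 12-month change is common, and MEDAS, BMI and measures at VT1 reappear among the secondary outcomes, to be analysed over time. This is true but does not settle the point. The primary test would still make no use of V1, and a SAP that only elaborates the published method would start from the same two-time-point analysis.

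**Conclusion.** The point holds as a free or cheap improvement to a method that the article does state, not as an error in it. The published primary analysis uses two time points, loses women without V2 unless their values are imputed, and leaves unused the 3-month data that exist for all three endpoints in both arms. Up to 110 of 600 women (18.3%) could be affected before the target of 490 is missed.

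How much this matters cannot be derived from the article. Under the adverse assumptions above, the completer estimate exceeded a true effect of 1.0 by about a third (1.34) when loss depended on the 3-month value, and by 0.63 when it depended on the unseen 12-month value. It was unbiased when loss was random or depended on baseline. The 0.2-point illustration is likewise an assumption. The documents do not support claiming a definite bias towards the intervention: withdrawal is named only as a possibility, contamination would act the other way, and the net direction is unknown.

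**What to change.** In the SAP, replace the two-time-point analysis of variance with a baseline-adjusted repeated-measures model (MMRM or constrained longitudinal data analysis):

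- Include all randomised women in their allocated arm. A woman with no value after baseline adds almost nothing to the estimate, but she stays in the defined population.
- Use SE, V1 and V2 only. Leave out the MEDAS values at V1-6 and V1-9, which exist in one arm only.
- Fit arm-by-visit terms, an unstructured covariance and the minimisation factors. Make the arm contrast at V2 the primary test for each endpoint, at the Bonferroni level already set.
- Add one delta-adjusted or control-based sensitivity analysis, because the main model relies on missing at random and cannot repair losses before V1.

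The cost is SAP wording and slightly more modelling work. No visit, measurement or woman is added. The downside is that the main result then rests openly on the missing-at-random assumption. When the article was published the SAP was still to be written and the trial was recruiting, so the change could be made before any data analysis.
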